# The effect of exercise rehabilitation with exergames combined with ice therapy in the treatment of obese patients with gout: protocol for a clinical trial

**DOI:** 10.1186/s13063-024-08237-z

**Published:** 2024-06-21

**Keywords:** Gout, Exergames, Ice therapy, BMI, Randomized controlled trial

## Abstract

**Background:**

Gout remains a leading cause of inflammatory arthritis worldwide, and the main risk factor for gout is persistent hyperuricemia. The clinical management of gout is mostly drug-based, and other treatment options are often ignored. This research proposal will explore whether exergames combined with ice therapy can help patients with gout to lose weight, relieve pain, improve the range of movement, improve quality of life, decrease uric acid level, decrease kinesiophobia and improve mental health of patients with gout.

**Methods:**

This experiment will use a two-arm randomized controlled design. The study setting is at the Advanced Medical and Dental Institute (AMDI), Universiti Sains Malaysia (USM). Obese patients with gout (*N* = 30) will be randomly assigned to the control group (receive an exergames intervention) and intervention group (receive an exergames intervention combined with ice therapy). The outcomes measurement will be conducted before (baseline) and after intervention (4 weeks). Then, it will be followed up at 12 weeks.

**Discussion:**

To our knowledge, no study has investigated the effect of exergames and ice therapy among gout patients. This study is expected to demonstrate that exercise rehabilitation facilitated by exergames with ice therapy is more effective in gout management compared to a conventional rehabilitation intervention.

**Trial registration:**

Chinese Clinical Trial Registry (ChiCTR2300070029). Registered on 31 March 2023.

## Introduction

### Background and rationale {6a}

Gout remains a leading cause of inflammatory arthritis worldwide, with persistent hyperuricemia being the main risk factor [1]. Hyperuricemia predisposes individuals to monosodium urate (MSU) crystal deposition in and around the joints [2]. Reducing inflammation and controlling symptoms are the most important intervention goals in gout patients [3]. The prevalence of gout is rising globally [4]. Obesity and aging are two risk factors significantly associated with the development of gout [5]. Therefore, the global rise in gout is considered more prevalent among aging populations and those with higher obesity rates [6]. Dasgupta et al. [7] conducted a study to investigate risk factors for recurrent gout attacks in Malaysian patients, and the findings showed that gout recurrence rates were 44% and 70% in non-obese and obese patients, respectively.

Exercise can effectively manage obesity associated with gout [8]. Additionally, regular and moderate exercise can produce measurable anti-inflammatory effects, reducing the annual frequency of gout attacks, alleviating joint swelling, and lowering pain scores in gout patients [9]. Although exercise is significant for patients with gout, joint pain and swelling caused by the deposition of uric acid crystals in the joints may reduce patients’ adherence to exercise. One strategy to promote exercise adherence in gout patients is the use of exergames. Exergames are technology-driven physical activities that integrate interactive gameplay into the exercise process [10]. Several studies have examined and demonstrated the benefits of exergaming, indicating the potential of using exergames as a viable intervention for increasing physical activity among the sedentary population [11].

Recovery from exercise is essential for a successful exercise intervention [12]. To avoid exacerbating joint inflammation caused by exercise, practitioners may want to consider treating gout patients with ice therapy after exercise. The application of ice therapy after exercise is reported to be beneficial in reducing muscle temperature and blood flow, thereby inhibiting the local inflammatory response [13]. Moreover, numerous studies indicate that ice therapy can alleviate delayed onset muscle soreness (DOMS) within 24 h following exercise [14]. Therefore, for gout patients who are prone to giving up exercise due to fear of worsening pain, ice therapy is a potential method to reduce patients’ kinesiophobia. In addition, the British Society for Rheumatology Guideline for the Management of Gout also suggests that ice could be an adjunct to acute gout treatment, as it can effectively reduce the symptoms in gout patients [1].

The prevalence of gout is showing an upward trend, and many patients’ symptoms are not well controlled [15]. Research has shown that despite the possibility of early diagnosis and understanding of risk factors, most patients continue to relapse after treatment and are at risk for further joint damage and other complications [16]. When asked about the adequacy of gout management and treatment, medical practitioners generally believe that treatment is adequate, while some patients believe it is not sufficiently managed [16].

### Objectives {7}

The clinical management of gout is primarily drug-based, and other treatment options are often ignored. This research aims to explore whether exercise using exergames combined with ice therapy can help patients with gout to lose weight, relieve pain, improve the range of movement, improve quality of life, decrease uric acid levels, decrease kinesiophobia, and improve the mental health of patients with gout. This potential gout management treatment is novel, economical, and easy to access.

**Fig. 1 Fig1:**
[figure not shown]
Flow chart of study

## Methods: participants, interventions, and outcomes

### Study setting {9}

The team members of the experiment include the lead investigator, who will record and organize measured data; a physical therapist, who will perform exercise rehabilitation and ice therapy on the participants; a therapist, who will supervise the intervention to ensure uniformity and standardization of treatment; an outcome measurer, responsible for outcomes measurement; and a gout expert, who will provide professional clinical judgment and respond to emergencies during treatment. The study will be conducted at the Advanced Medical and Dental Institute (AMDI), Universiti Sains Malaysia (USM). The participants will register under the exercise clinic, AMDI USM, Malaysia.

### Eligibility criteria {10}

Participant selection will be conducted by attending professionals. The diagnosis of gout refers to the 2015 Gout Classification Criteria developed by the American College of Rheumatology (ACR) and the European League of Associations for Rheumatology (EULAR) [17].

#### Inclusion criteria

The participants must:Have ages ranging from 18 to 70Have BMI ≥ 25Can participate in treatment independentlyLive in the local area, will not travel far during treatmentMeet the preliminary criteria for classifying the acute arthritis of primary gout

#### Exclusion criteria

The participants will be excluded if they are:Patient with the current of urate-lowering therapy (ULT)Patients without gout-related pain or with mild painPregnant womanPatients with serious heart or vascular diseasePatients with mental problems or a history of mental illnessNot meeting the preliminary criteria for classifying the acute arthritis of primary goutPatients who do not meet obesity criteriaPatients have a serious medical condition that precludes exercise intervention

### Who will take informed consent? {26a}

Subjects participating in the study will be recruited from ADMI clinics, and advertisements containing detailed research information will be disseminated through ADMI clinic physicians and social media. Before study participation, all subjects will be required to sign an informed consent form. The procedure for obtaining informed consent will be conducted by two experienced physicians ([name] and [name]) at the ADMI clinic. This procedure will include providing potential participants with the informed consent form and allowing them sufficient time to read the entire document. Additionally, the physicians will thoroughly explain the trial’s interventions, objectives, potential risks, and benefits.

### Additional consent provisions for collection and use of participant data and biological specimens {26b}

This study will request consent to collect participants’ blood samples to assess fasting blood glucose, total cholesterol, triglyceride, high-density lipoprotein (HDL) cholesterol, low-density lipoprotein (LDL) cholesterol, urea, creatinine, estimated glomerular filtration rate (eGFR), and uric acid levels.

### Interventions

#### Explanation for the choice of comparators {6b}

The aim of this study is to evaluate the efficacy of exergames combined with ice therapy, using exergames alone as the comparator. Innovative exergames hold promise for engaging participants in increased physical activity and may offer benefits for highly sedentary individuals or those averse to conventional exercise modalities [18]. Previous studies have shown that exergames have significant effects in reducing BMI, increasing physical activity levels, improving cardiovascular risk factors, and enhancing psychological health [19, 20].

#### Intervention description {11a}

##### Control group

Participants in the intervention group will be asked to receive an exergames intervention for 40 min a day, 3 to 5 days a week, at least 120 min per week, for 4 weeks. The target HRmax should be between 64 and 76% for moderate exercise intensity. The exergames intervention will be facilitated by cardio-respiratory exercise games (Ring Fit Adventure, Mario Tennis Aces, Sports Party, Fit’s Island Cycling, and Aerobic Step) from Nintendo. Patients can choose exergames to achieve a target heart rate according to their preferences. Participants must wear a heart rate monitor during exercise to achieve the target heart rate. In addition to applying heart rate as an objective indicator of exercise intensity, the Borg Rating of Perceived Exertion (RPE) will be applied to measure the individual’s perception of exercise intensity. Participants will be asked to achieve moderate-intensity exercise on a Borg scale of 10 to 13.

##### Intervention group (exergames + ice therapy)

Participants in the intervention group will be asked to receive an exergames intervention for 40 min a day, 3 to 5 days a week, at least 120 min per week, for 4 weeks. The target HRmax should be between 64 and 76% for moderate exercise intensity. Exergames intervention will be facilitated by cardio-respiratory exercise games (Ring Fit Adventure, Mario Tennis Aces, Sports Party, Fit’s Island Cycling, and Aerobic Step) from Nintendo. Participants must wear a heart rate monitor during exercise to achieve the target heart rate. In addition to applying heart rate as an objective indicator of exercise intensity, the Borg Rating of Perceived Exertion (RPE) will be applied to measure the individual’s perception of exercise intensity. Participants will be asked to achieve moderate-intensity exercise on a Borg scale of 10 to 13.

Moreover, the patients will also be treated with ice therapy, utilizing circular localized massage with ice bags made of polyethene plastic on key muscles of the upper and lower extremities that are prone to muscle damage and lactic acid accumulation during exercise as well as on critical joints prone to gout attacks. The duration of ice therapy will be 15 to 20 min after exergames intervention.

To rule out the influence of dietary choices, the researchers will ask all participants to maintain a low-purine diet and abstain from alcohol during the exercise intervention. Moreover, participants will be asked to record their daily intake in diaries. The researcher will regularly monitor and check the diaries to ensure adherence to dietary guidelines.

#### Criteria for discontinuing or modifying allocated interventions {11b}

Adverse events: If a participant experiences severe adverse events or side effects directly attributed to the allocated intervention, the intervention may be discontinued or modified as necessary for the participant’s safety. The decision will be based on clinical judgment and in consultation with the study’s principal investigator and relevant medical professionals.Participant withdrawal of consent.The participant fails to comply with the study requirements or guidelines related to the allocated intervention.Changes in the participant’s health status or external factors affecting the study may warrant modification or discontinuation of the allocated intervention.

#### Strategies to improve adherence to interventions {11c}

To improve adherence to the intervention, each participant will receive a transportation subsidy and a free medical screen.

#### Relevant concomitant care permitted or prohibited during the trial {11d}

Participants will not be eligible for the study if they are expected to require additional urate-lowering medication during the trial phase.

#### Provisions for post-trial care {30}

This trial does not provide post-trial care.

### Outcomes {12}

The primary and secondary outcomes of the study will be measured at three time points: baseline (0 weeks), post-intervention (4 weeks), and follow-up (12 weeks). All measurements will be taken at the same location and performed by the same therapist. All data will be collected by a designated investigator and recorded in Microsoft Excel.

#### Primary outcomes

Anthropometric parameters: body mass index **(**BMI)Biochemical indicators: the concentration of serum uric acid (SUA)

#### Secondary outcomes

Anthropometric parameters: waist circumference (WC), hip circumference (HC), waist-to-hip ratio, range of movement in target joinBiochemical indicators: fast blood glucose, total cholesterol (TC), triglyceride, high-density lipoprotein (HDL) cholesterol, low-density lipoprotein (LDL) cholesterol, uric acid (UA), and creatininePhysiological indicators: systolic blood pressure (SBP), diastolic blood pressure (DBP)Subjective indicators: pain intensity (24 h after exercise, measurement tool: visual analogue scale (VAS)), gout-specific quality of life (measurement tool: The Gout Impact Scale (GIS)), kinesiophobia (measurement tool: The Tampa Scale of Kinesiophobia (TSK)), positive and negative affect of exercise (measurement tool: Positive and Negative Affect Schedule (PANAS))Adverse effect: rate of gout flare

### Participant timeline {13}

The schedule of enrollment, interventions, and assessments is shown in Fig. 2.

**Fig. 2 Fig2:**
[figure not shown]
Schedule of enrollment, interventions, and assessments

### Sample size {14}

The sample size was calculated using GPower. This study is a randomized controlled trial with an equal number of subjects in the intervention and control groups. The primary outcome measure was the serum uric acid concentration. According to previous studies [21], the serum uric acid concentration of patients in the control group was 420 ± 100 µmol/L. The effect size was set to 0.25, bilateral *α* = 0.05 was set, and the power was 80%; at least 14 patients will be included in each group, making the sample size *N* = 28. Considering a 10% follow-up dropout rate, at least 30 patients will be included, with a minimum of 15 patients in each group.

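### The 80% power statement rests on an unlabelled effect size of 0.25 that, on the only reading found to give N = 28, implies an unstated serum uric acid difference of about 106 to 120 µmol/L; 30 patients also fall just short of the stated 10% loss

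*Protocol article*

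**What the plan says.** Sample size {14} of the protocol article sizes the trial on SUA: "The primary outcome measure was the serum uric acid concentration". It cites earlier work for the control arm: "the serum uric acid concentration of patients in the control group was 420 ± 100 µmol/L". It then says "The effect size was set to 0.25", adds "bilateral *α* = 0.05 was set" and a power of 80%, and concludes "at least 14 patients will be included in each group, making the sample size *N* = 28". For attrition it says: "Considering a 10% follow-up dropout rate, at least 30 patients will be included, with a minimum of 15 patients in each group".

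The section gives no target SUA difference, no intervention-arm mean, no label for the effect size (standardised mean difference d, or Cohen's f), no test and no correlation between repeated measurements.

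Other sections supply part of this. Outcomes {12} sets measurements at weeks 0, 4 and 12. Statistical methods {20a} plans a two-way repeated measures ANOVA and excludes patients who do not complete. Trial design {8} calls the framework exploratory.

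**The concern.** A mean, an SD and an effect size printed together look like the inputs to the sample size. Beside an SD of 100 µmol/L, an unlabelled 0.25 is naturally taken as 0.25 SD, or 25 µmol/L, and 14 per arm is far too few for that. If 0.25 is instead Cohen's f in a repeated measures design, N = 28 is understandable, but the difference it stands for is more than four times as large, and the article never converts it to µmol/L.

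What is at stake is how the result is read. Both arms receive the same exergames prescription, so the contrast is the ice therapy alone. A reader who relies on the 80% figure without knowing the size of the effect behind it could take a non-significant SUA result as evidence that ice adds nothing, when the trial had little chance of detecting a moderate difference. The Discussion raises the stakes, since it foresees the results guiding the choice of exercise programme.

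**Working it through.** **Inputs from the article.** SD 100 µmol/L, effect size 0.25, two-sided α = 0.05, power 80%, 14 per arm, 10% loss, 30 enrolled (Sample size {14}); 3 measurements at weeks 0, 4 and 12 (Outcomes {12}); two-way repeated measures ANOVA (Statistical methods {20a}).

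**Assumptions, not in the article.** Correlation ρ = 0.5 between measurements, varied below; sphericity (ε = 1); equal baselines in the two arms.

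**1. Reproducing N = 28.** For the group-by-time interaction with N patients and m measurements, λ = f²·N·m/(1 − ρ), with m − 1 and (N − 2)(m − 1) degrees of freedom.
- f = 0.25, N = 28, m = 3, ρ = 0.5: λ = 0.0625 × 28 × 3/0.5 = 10.5, df 2 and 52, power 0.812.
- N = 26 gives 0.778, so 28 is the smallest even N reaching 80%.

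The figure reproduces, and the test fits the planned analysis. Neither 420 nor 100 enters the formula.

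**2. Other readings of 0.25 that were tried.**

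| Reading | Total N for 80% power |
|---|---|
| d = 0.25 (25 µmol/L), two-sample t-test | 506 (253 per arm) |
| f = 0.25 in a two-group comparison (d = 0.5) | 128 (64 per arm) |
| 25% of 420 = 105 µmol/L, t-test | 32 (16 per arm) |
| Interaction, 2 measurements, ρ = 0.5 | 34 |
| Between-group factor, 3 measurements, ρ = 0.5 | 86 |
| Interaction, 3 measurements, SPSS-type f | 82 |

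None gives 28. With 14 per arm, a t-test for d = 0.25 has a noncentrality of 0.25 × √(14/2) = 0.661 on 26 df and power of about 10%.

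**3. What f = 0.25 means in µmol/L.** If the between-arm difference follows a pattern p over the three visits, in units of its largest value, then f per SD of difference is the root mean square of (p − mean of p)/2.
- Sustained at weeks 4 and 12, p = (0, 1, 1): √(1/18) = 0.2357, so 0.25/0.2357 = 1.06 SD, or 106 µmol/L.
- Linear over weeks 0, 4 and 12, p = (0, 1/3, 1): 0.2079, so 0.25/0.2079 = 1.20 SD, or 120 µmol/L.

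As a cross-check, a single two-sided t-test with 14 per arm has 80% power at 1.10 SD (110 µmol/L).

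**4. Power at N = 28 for smaller sustained differences.** Here f = 0.2357 × d.

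| Difference | f | ρ = 0.5 | ρ = 0.7 |
|---|---|---|---|
| 25 µmol/L (d = 0.25) | 0.059 | about 9% | about 13% |
| 50 µmol/L (d = 0.5) | 0.118 | about 24% | about 39% |

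**5. Dependence on the correlation, f = 0.25, N = 28.** Power is 66% at ρ = 0.3, 81% at 0.5 and 96% at 0.7. At ρ = 0.7 a sustained difference of about 82 µmol/L has 81% power.

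**6. Dropout.** 30 × 0.9 = 27, below 28. The required enrolment is 28/0.9 = 31.1, or 32 with equal arms. Thirty patients tolerate a loss of 2, and 2/30 = 6.7%. At N = 27 under the model in step 1, λ = 10.125 and power is 79.5%.

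**The case against.** The strongest reply is that the calculation is not wrong. N = 28 and 80% power reproduce with a test that matches the article's own design: two groups, three visits, repeated measures ANOVA. What is absent is the f label, the correlation and the sphericity value, and a journal article may leave such software settings to the full protocol. The detectable difference also depends on a correlation nobody outside the team knows; at 0.7 the trial does better than the 80% claimed. The dropout gap costs less than two percentage points of power, and the trial is declared exploratory.

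Most of this stands. A reader might infer that the sample size is an arithmetic error and that 253 per arm are needed. The article does not support that: it states no 25 µmol/L target and names no t-test, and the d = 0.25 reading conflicts with its planned analysis. Nor does it follow that more patients must be recruited.

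Two things remain. First, the complaint goes beyond missing settings: the section prints a mean and SD as if they led to N = 28, and they do not. Second, the exploratory label does not cancel an explicit 80% power statement, least of all when the Discussion expects the trial to demonstrate superiority.

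**Conclusion.** The point holds as a fault in how the power claim is stated, not as a miscalculated N. The printed SUA figures do not produce "at least 14 patients will be included in each group". The only reading found that does implies a between-arm difference of about 1.06 to 1.20 SD (106 to 120 µmol/L, or 25 to 29% of 420), which is neither stated nor justified. Against a sustained 50 µmol/L the trial has roughly a one in four chance of significance at correlation 0.5, and about 39% at 0.7.

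These figures assume equal baselines, sphericity, an SD of 100 µmol/L at every visit and the correlations shown. The settings in step 1 are inferred from the result, so they may not be what the authors entered.

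The dropout sentence is wrong on its own terms (27 against 28) but secondary. Severity: should be fixed.

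**What to change.** Revise the text of Sample size {14}:

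- State the test, effect-size metric, number of measurements, correlation and sphericity value actually used in the software. The authors should report their own settings and not adopt the ones inferred here.
- Give the implied SUA difference in µmol/L and the pattern over weeks 0, 4 and 12 that it assumes. If 420 ± 100 is kept, say what it is used for.
- Restate power for smaller differences such as 25 and 50 µmol/L, each with its assumed correlation.
- Say that a non-significant result in this exploratory trial is not evidence of no effect.
- Correct the dropout sentence to say that 30 allows for the loss of 2 patients (6.7%), and that 27 remain at 10% loss.

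The cost is a text correction and a less favourable power statement. No extra patients and no change to trial conduct are needed.

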### Recruitment {15}

Participants will be recruited at ADMI between June 2023 and September 2024. Researchers will access the medical records of gout patients within the ADMI system. Once eligibility is confirmed, potential participants will be contacted by phone to inquire about their willingness to participate in the study. Additionally, clinic physicians will distribute study advertisements to eligible gout patients.

## Assignment of interventions: allocation

### Sequence generation {16a}

Participants will be randomly assigned to either the control group and intervention group in a 1:1 ratio by a researcher using computer-generated random numbers table. Each participant will receive a unique number, which will then be matched with a corresponding group assignment (either control or intervention) based on the random number table. The researcher will prepare 30 sealed envelopes and place randomly generated serial numbers inside them in order.

